## Abstract

**Background:**

Stress fractures are a common and potentially debilitating overuse injury to bone and occur frequently among military recruits and athletes. Recovery from a lower body stress fracture typically requires several weeks of physical rehabilitation. Teriparatide, a recombinant form of the bioactive portion of parathyroid hormone (1–34 amino acids), is used to treat osteoporosis, prevent osteoporotic fractures, and enhance fracture healing due to its net anabolic effect on bone. The study aim is to investigate the effect of teriparatide on stress fracture healing in young, otherwise healthy adults undergoing military training.

**Methods:**

In a two-arm, parallel, prospective, randomised controlled, intention-to-treat trial, Army recruits (*n* = 136 men and women, 18–40 years) with a magnetic resonance imaging (MRI) diagnosed lower body stress fracture (pelvic girdle, sacrum, coccyx, or lower limb) will be randomised to receive either usual Army standard care, or teriparatide and usual Army standard care. Teriparatide will be self-administered by subcutaneous injections (20 μg/day) for 16 weeks, continuing to 24 weeks where a fracture remains unhealed at week 16. The primary outcome will be the improvement in radiological healing by two grades or more, or reduction to grade zero, 8 weeks after randomisation, assessed using Fredericson grading of MRI by radiologists blind to the randomisation. Secondary outcomes will be time to radiological healing, assessed by MRI at 8, 10, 12, 14, 16, 20 and 24 weeks, until healed; time to clinical healing, assessed using a clinical severity score of injury signs and symptoms; time to discharge from Army physical rehabilitation; pain, assessed by visual analogue scale; health-related quality of life, using the Short Form (36) Health Survey; and adverse events. Exploratory outcomes will include blood and urine biochemistry; bone density and morphology assessed using dual-energy X-ray absorptiometry, peripheral quantitative computed tomography (pQCT), and high-resolution pQCT; physical activity measured using accelerometers; and long-term future fracture rate.

**Discussion:**

This study will evaluate whether teriparatide, in addition to standard care, is more effective for stress fracture healing than standard care alone in Army recruits who have sustained a lower body stress fracture.

**Trial registration:**

ClinicalTrials.govNCT04196855. Registered on 12 December 2019.

## Administrative information

The order of the items has been modified to group similar items (see http://www.equator-network.org/reporting-guidelines/spirit-2013-statement-defining-standard-protocol-items-for-clinical-trials/).

## Introduction

### Background and rationale {6a}

Stress fractures are a common and potentially debilitating overuse injury to bone and are frequently reported among military recruits and athletes [1–6]. Bone normally remodels through a continual, balanced cycle of osteoclastic resorption and osteoblastic bone formation. Sudden increases in training volume of high-intensity, repetitive impact activities (e.g. running and marching) without adequate time for recovery can cause an imbalance in bone remodelling [7], with greater osteoclastic activity at the sites of mechanical loading causing a weakening of the bone, microdamage, and a subsequent stress fracture [5, 8]. Stress fracture injuries can lead to a full fracture without a significant reduction in physical activity levels and a period of rehabilitation [9]. Lower body (i.e. pelvic girdle, sacrum, coccyx, and lower limb) stress fractures require the longest rehabilitation times of all musculoskeletal injuries sustained during Army Infantry training, often exceeding 80 days [2]. The return to training of athletes who have sustained lower body stress fractures takes between 61 and 153 days, on average [6].

Daily subcutaneous injections of teriparatide, a recombinant form of the bioactive portion of parathyroid hormone, containing the first 34 amino acids, have been used to treat osteoporosis, prevent osteoporotic fractures and enhance fracture healing due to its net anabolic effect on bone [10–12]. Continuous infusion of teriparatide has a catabolic effect on bone, whereas intermittent daily injections have an anabolic effect [13–17]. Accelerated bone remodelling, earlier replacement of woven bone with lamellar bone, and improvements in mechanical strength, bone mineral content, and callus volume and strength have been documented after the administration of teriparatide in animal models of fracture healing (e.g. long bones of rat, mouse, rabbit, monkey [10]). A number of studies conducted in postmenopausal women and osteoporotic patients have demonstrated increased bone mineral density [18–21], bone mineral content [20–22], and an increase in biochemical markers of bone formation and resorption [18, 19, 23] following treatment with teriparatide. Pain in limb (reported by ≥ 10% of patients), followed by nausea, headache, and dizziness (each reported by ≥ 1% to < 10% of patients) are the most common adverse reactions to teriparatide [24]; nevertheless, treatment with teriparatide in humans is considered safe [24–26]. In randomised controlled trials, 8 weeks of daily teriparatide accelerated fracture healing in postmenopausal women [27], and parathyroid hormone [1-84] accelerated fracture healing and reduced pain after 8 weeks, and improved mobility in elderly osteoporotic women (aged > 70 years) [28]. No effect of teriparatide on fracture healing or pain was observed in two randomised controlled trials treating men and postmenopausal women (aged ≥ 50 years) [29, 30], but the treatment was limited to 4 weeks [29], and the trials were underpowered [29, 30]. Randomised controlled trials comparing teriparatide with bisphosphonates reported increased bone mineral density and decreased fracture risk with teriparatide use in postmenopausal osteoporosis patients [31], but variable effects on radiological healing, pain, and quality of life have been observed in men and women [32, 33]. The assessment of different outcome measures and inclusion of various fracture types might be responsible for these variable responses to teriparatide compared with bisphosphonates. Teriparatide reduced the risk of future fractures compared with placebo in postmenopausal women with prior fractures [20, 34], but no studies have examined this effect in young adults.

Only one published randomised controlled pilot study has examined the effect of teriparatide on stress fracture healing in young adults (aged 21–45 years) [35]. Using Fredericson grading of magnetic resonance imaging (MRI) to assess the healing of lower limb fractures, four women (67%) who received teriparatide for 8 weeks, compared with three women (43%) in the placebo control group, achieved a two grades or more improvement in healing or reduction to grade zero. Biochemical markers of bone formation increased more in women who received teriparatide compared with placebo [35], indicating a significant anabolic window, whereby teriparatide initially stimulates bone formation, with a rapid increase in bone formation markers during the initial weeks, followed by increases in bone resorption markers in later weeks [36]. A number of case studies of young and elderly adults (32–91 years) support the efficacy of teriparatide for accelerating fracture [10] and stress fracture healing [37]. Despite these encouraging findings, the effectiveness of teriparatide for promoting fracture healing remains unclear, particularly among young, otherwise healthy adults. High quality randomised controlled trials are required to test the efficacy of teriparatide for stress fracture healing.

Optimising the healing of stress fractures is relevant to the military training environment because quality of healing, time to fracture union and return to training can have significant consequences for military recruits in terms of career progression, and risk of re-injury and medical discharge, and the Ministry of Defence in terms of the cost of working days lost in rehabilitation and loss of recruits from training. Changes to initial military training intended to reduce the risk of musculoskeletal injury have mostly been ineffective [2]. Effective strategies for optimising the rehabilitation of stress fracture injuries and expediting a return to training will improve the overall health and wellbeing of individuals and may also reduce medical attrition rates. The aim of the present study is to evaluate the effect of daily teriparatide injections on lower body stress fracture healing in young, otherwise healthy adults undergoing Army training.

### Objectives {7}

The primary objective of the RETURN trial is to investigate the effect of teriparatide in addition to usual Army standard care on lower body stress fracture healing in military recruits, compared with usual Army standard care alone. The primary outcome will be the improvement in radiological healing, assessed using Fredericson grading of MRI, by two grades or more, or reduction to grade zero, 8 weeks after randomisation. Secondary objectives are to examine the effect of teriparatide on (i) time to radiological healing; (ii) time to clinical healing, assessed by clinical severity score calculated from injury signs and symptoms; (iii) time to discharge from Army physical rehabilitation; (iv) pain symptoms; (v) health-related quality of life; and (vi) adverse events. It is hypothesised that treatment with teriparatide will accelerate (i) the rate of radiological healing of lower body stress fractures; (ii) the cessation of pain associated with the injury; and reduce (iii) the time taken to return to Army training, compared with standard care alone. The effect of teriparatide on the following exploratory outcomes will also be investigated: (i) blood and urine biochemistry; (ii) bone density and morphology; (iii) physical activity levels; and (iv) long-term future fracture rate.

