##### Time to clinical healing

Clinical healing assessments will commence twice weekly after a participant has been classified as radiologically healed, using a protocol based on the index developed by Beck et al. 2012 [41]. A clinical severity score will be calculated from seven sign and symptom scores: (i) pain during daily activities; (ii) night pain; pain when (iii) running and (iv) hopping; and (v) local tenderness, (vi) pain during percussion, and (vii) local swelling of soft tissue, each at the site of the stress fracture. Clinical assessments will cease when a clinical severity score of zero (i.e. healed) has been achieved. The time from randomisation to clinical healing will be analysed.

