##### Pain symptoms

Participants will rate the level of pain they are feeling on a visual analogue scale once-a-week for the duration of their participation in the study [42, 43]. Pain scores will be analysed as a change from baseline.

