### Sample size {14}

A total sample size of 136 participants will be required (68 participants per trial arm, prior to accounting for drop-out), based on the primary outcome of an improvement in radiological healing by two Fredericson grades or more, or reduction to grade zero, 8 weeks after randomisation. The sample size was determined using data from Almirol and colleagues’ (2016) 8 week randomised controlled trial in adults aged 21–45 years with recent lower-extremity stress fractures (35). Almirol et al. (2016) reported 67% of participants who received teriparatide achieved a two grades or more improvement in healing or reduction to grade zero (i.e. ‘success’); compared with 43% of participants in the placebo group [35]. Assuming a 20% drop-out rate during the first 8 weeks of the present study, 108 participants (54 participants per trial arm) will complete an MRI scan at week 8; thereby providing 80% statistical power to detect a between group difference (two-sided test, significance level of 5%), if the ‘success’ rate is ≥ 71% in the intervention arm (chi-squared test with continuity adjustment). This equates to an odds ratio of 3.23 or a relative increase in healing of approximately 65%.

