## Statistical methods

### Statistical methods for primary and secondary outcomes {20a}

A full statistical analysis plan (SAP) will be developed by the Trial Statistician and Chief Investigator before the final data lock and will be submitted to the independent Data Monitoring Committee (DMC) and Trial Steering Committee (TSC) for approval [48]. The primary efficacy analysis will be based on the intention-to-treat principle in which all participants will be analysed according to the trial arm to which they were allocated, regardless of compliance. The primary outcome (radiological healing by two Fredericson grades or more, or reduction in grade to zero, 8 weeks after randomisation) will be analysed using a logistic regression model. This model will include the baseline stratification variables (vitamin D status and single or multiple lower body stress fractures); anatomical site of fracture; baseline MRI grade; allocated trial arm; and any other baseline prognostic variables pre-specified in the SAP. The estimate of efficacy will be the between group difference from the analytical model, calculated with 95% confidence intervals and with statistical significance set at the 5% level (two-sided). Secondary outcomes will be analysed in an analogous manner, i.e. using appropriate statistical models with stratification variables, additional specific prognostic variables (including the baseline value of the outcome where available) and allocated trial arm. A secondary analysis of MRI grading at each time point using a logistic regression model with a generalised estimating equation approach to parameter estimation and a specified auto-regressive correlation structure, i.e. to allow for the correlation in outcome between timepoints, will also be completed.

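### The pain hypothesis is about when pain stops, but the weekly pain scores are to be analysed only as change from baseline, which does not test that directly

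*Protocol article*

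**What the plan says.** Objectives {7} gives three hypotheses. Teriparatide is expected to speed up (i) radiological healing and (ii) "the cessation of pain associated with the injury", and to shorten (iii) the time to return to Army training. The secondary objectives in the same section are worded differently: the first three are times to an event, while pain appears without any reference to time, in the run "iii) time to discharge from Army physical rehabilitation; (iv) pain symptoms; (v) health-related quality of life; and (vi) adverse events".

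Pain symptoms, under Outcomes {12}, sets the measurement: "Participants will rate the level of pain they are feeling on a visual analogue scale once-a-week for the duration of their participation in the study". It then fixes the variable: "Pain scores will be analysed as a change from baseline".

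Statistical methods {20a} says that secondary outcomes will be analysed "using appropriate statistical models with stratification variables, additional specific prognostic variables (including the baseline value of the outcome where available) and allocated trial arm". It names no visit, model or summary for pain.

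Time to clinical healing uses a severity score built from seven signs and symptoms, several of them pain items. "Clinical healing assessments will commence twice weekly after a participant has been classified as radiologically healed", and "The time from randomisation to clinical healing will be analysed".

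**The concern.** Hypotheses (i) and (iii) each have a matching outcome counted from randomisation: time to radiological healing and time to discharge from rehabilitation. Hypothesis (ii) has no such outcome on the pain scale. A difference in mean change says that one arm had less pain on average. It does not say that pain ended sooner. Two arms can differ in mean change because pain is milder while it lasts, with no difference in when it ends. They can also show the same mean change at a late visit although one arm became pain free weeks earlier.

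At stake is whether the report can speak to its own hypothesis. Without a defined cessation event, a claim of faster pain cessation would have to be inferred from a mean-change result, or would rest on a definition chosen after the data are seen.

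**Working it through.** **Step 1. Set the sections side by side.**

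| Hypothesis (Objectives {7}) | Outcome that dates the event | Match |
|---|---|---|
| (i) faster radiological healing | time from randomisation to Fredericson grade zero | yes |
| (ii) faster end of pain | none on the VAS; time to clinical healing in part | partial |
| (iii) shorter time to return to training | time from randomisation to the initial discharge decision | yes |

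Clinical healing is only a partial match for two reasons. First, it is a composite of seven items: five of pain (daily activities, night, running, hopping, percussion), one of tenderness and one of swelling, so swelling alone delays the event. Second, its assessments start only after radiological healing, and MRI is first repeated at week 8. Pain that ends before week 8, or while MRI is still abnormal, cannot be dated by it. The weekly VAS can date such pain.

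**Step 2. The plan's own figure.** Sample size {14} gives no figure for pain. The primary calculation (43% v 71%, 54 completers per arm, continuity adjustment) supplies the number per arm used below, so I checked it.
- Numerator: 0.28 − 1/54 − 1.96 × √(2 × 0.57 × 0.43 / 54) = 0.28 − 0.0185 − 0.1867 = 0.0747
- Denominator: √((0.43 × 0.57 + 0.71 × 0.29)/54) = 0.0914
- Power = Φ(0.0747/0.0914) = Φ(0.818) = 79.3%, against the stated 80%
- Dropout: 68 × 0.80 = 54.4

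The stated figure reproduces.

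**Step 3. Precision of a time-to-cessation comparison.** The documents give no pain mean, SD, resolution time or hazard ratio (HR), so every input here is an assumption. By Schoenfeld's formula, power = Φ(√(d/4) × ln HR − 1.96). With d = 108 (every completer reaches cessation, an upper limit), √(108/4) = 5.196.
- HR 1.5: Φ(2.107 − 1.96) = 56%
- HR 1.75: Φ(2.908 − 1.96) = 83%
- HR 2.0: Φ(3.602 − 1.96) = 95%

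**Step 4. Does change from baseline lose power?** First simulation: 1,500 trials, 54 per arm, VAS 0–100, baseline mean 50 and SD 20, linear decline to zero, Weibull cessation times (shape 1.5), HR 1.75, scores exactly zero after cessation. The log-rank test is on the first pain-free week; change is adjusted for baseline.

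| Control median | Log-rank | Change wk 4 | wk 8 | wk 12 | wk 16 | Mean change wks 1–16 |
|---|---|---|---|---|---|---|
| 6 weeks | 81% | 60% | 62% | 38% | 8% | 72% |
| 12 weeks | 72% | 45% | 60% | 64% | 60% | 67% |

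With a 6-week median, 86% of controls are pain free at week 12 and 95% at week 16, which is why late visits carry little information. Against the average over all weeks, the gap is only 81 − 72 = 9 and 72 − 67 = 5 points. Across control medians of 4 to 12 weeks and HR 1.75 to 2.0 it runs from 3 to 9 points.

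**Step 5. Is that small gain robust?** Second set of assumptions: baseline mean 45 and SD 18, Weibull shape 2, rating noise SD 6, control median 9 weeks, HR 1.6.
- Scores exactly zero after cessation: two consecutive zeros 64%, mean change 56%.
- Rating noise continuing after cessation: two exact zeros 32%, mean change 54%. Replacing exact zero by a threshold of 5 or 10 brings the time-to-cessation test back to about 52%.
- Control median 14 weeks, exact zeros: two zeros 50%, mean change 53%.

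The advantage of the time-to-event test therefore vanishes or reverses under plausible rating noise or slow resolution. A definition based on exact zero is fragile; a small threshold largely removes the problem.

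**The case against.** The strongest reply is that objective and outcome already agree. The objective is simply pain symptoms, and change from baseline serves it. The mismatch is then with one sentence of hypotheses, which rewording would cure. This stands, and rewording is offered below as an equal remedy.

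A second reply is that pain does enter a time-to-event outcome through clinical healing. This stands in part. A reader might infer that the trial cannot confirm or refute hypothesis (ii) at all. The documents do not support that: clinical healing requires that injury-site pain be absent, and a change averaged over weeks gives indirect evidence of faster resolution. What is missing is a direct test.

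A third reply is that visit, model and derived variables belong in the SAP, which is not shown. For visit and model this is right, and neither is criticised here. The variable, however, is fixed in the protocol article, and it is the variable that does not match the hypothesis.

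A reader might also infer that the planned analysis is underpowered. That too is unsupported. Pain symptoms fixes no visit, so a single late-visit comparison is not what the plan prescribes. The simulated data also follow proportional hazards for cessation, which favours the log-rank test from the outset.

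**Conclusion.** The point holds as a mismatch between hypothesis and analysis variable. Hypothesis (ii) concerns when pain stops, the VAS variable concerns pain level, and clinical healing bridges the two only partly. This rests on the text alone and on no assumption.

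No general power gain should be claimed for a time-to-cessation analysis. Under assumed inputs, the loss from using change is large only at a single late visit when pain resolves quickly (8% against 81% at week 16). Against a longitudinal average it is at most about 10 points, and it can vanish or reverse. The case for the change is that it answers the stated question, and that the weekly scores are already collected in everyone.

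This is a minor, inexpensive improvement to a secondary outcome. The primary outcome and the sample size are not affected.

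**What to change.** Choose one of two routes before data lock.

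**Route A: add a direct test.** Keep change from baseline, over all weekly scores, as the pain analysis for objective (iv). Add time from randomisation to pain cessation for hypothesis (ii), specified as follows:
- Event: the first of two consecutive weekly scores at or below a small pre-specified VAS threshold, rather than exactly zero.
- Population: participants above that threshold at baseline.
- Censoring: at week 16, because the schedule in Fig. 2 continues beyond it only for unhealed fractures, so later scores come from a group selected by healing.
- Comparison: discrete-time model or log-rank test, adjusted for or stratified by vitamin D status and single or multiple fracture sites.
- Sensitivity analysis: use the analgesic intake already recorded in the diary, since a low score may reflect analgesia.

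**Route B: reword.** Change hypothesis (ii) to reduction in pain and add no analysis.

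Route A needs no new data: one derived variable, one analysis and one sensitivity analysis. Its costs are one more secondary result, a threshold that must be chosen and justified in advance, and the exclusion from this analysis of anyone already at or below the threshold at baseline. Because scores are self-reported in an open-label trial, the result should be read with that limitation, as should change from baseline. Route B costs nothing but gives up any direct statement about the timing of pain relief.

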### Trial design {8}

The RETURN trial is a phase III, multicentre, open label, two-arm parallel, prospective, randomised controlled trial (Fig. 1). A 1:1 allocation ratio will be used in this intention-to-treat, superiority trial.

**Fig. 1 Fig1:**
[figure not shown]
Overview of the trial design, interventions and assessments. ^1^Serum 25-hydroxyvitamin D < 30 nmol/L, deficient; ≥30 nmol/L, not deficient; ^2^Pregnancy test for all at baseline, week 16 and 24, and four-weekly for participants allocated to the intervention arm; ^3^Weekly visual analogue scale; ^4^Short Form (36) Health Survey; ^5^Dual-energy X-ray absorptiometry (DXA) scan of the lumbar spine and hips (baseline and week 16 only); peripheral quantitative computed tomography (pQCT) scan of the diaphyseal tibia; and high-resolution pQCT (HR-pQCT) scan of the metaphyseal tibia and radius; ^6^Accelerometer worn 24 h/day and replaced four-weekly; ^7^Columbia-Suicide Severity Rating Scale (C-SSRS) for all at baseline, and four-weekly for participants allocated to the intervention arm; ^8^Review of Army fitness records; ^9^Magnetic resonance imaging (MRI) scans to cease when fracture is radiologically healed; ^10^Clinical assessments twice weekly after fracture is radiologically healed, and to cease when fracture is clinically healed; ^11^Review of Army medical records

